### **Post-operative follow-up**

#### 3 ( $\pm$ 1) hours after end of surgery

- Surgery stop time will be registered in the CRF
- The estimated intra-operative and post-operative blood loss volumes will be registered in the blood loss log.
- Any allogeneic and/or autologous blood transfusions will be registered in the allogeneic and/or the autologous transfusion logs.
- The Sangvia® postoperative drain (test group) and the Bellovac drain (control group) connection time will be registered.
- Venous blood sample/s will be taken from each subject before return of post-operative autologous blood if applicable for analyses of Hb, Hct/EVF,  $\text{Na}^+$ ,  $\text{K}^+$ , TPC, CRP, LPC, creatinine and Glomerular Filtration Rate (GFR)/Creatinine Clearance ( $\text{C}_{\text{Cr}}$ ).
- For the patients randomized to the Sangvia® treatment group postoperative blood salvage will be stopped, returned and the kit disconnected within 6 hours after activation. The drain will remain connected until the first post-operative day. In total, the transfusion volume of 2500 ml must not be exceeded when combining the intra- and postoperatively collected autologous blood.
- Drainage will continue in both treatment groups.
- Any allogeneic and/or autologous blood transfusions will be registered in the allogeneic and/or the autologous transfusion logs.
- Presence of SIRS will be evaluated.

- Vital signs (blood pressure, body temperature and heart rate) will be registered.
- Any additional adverse events and/or medications will be registered in applicable logs.
- Clinical signs or symptoms of general and/or wound infection will be registered.

Day 1 - first post-operative morning, 24 ( $\pm 6$ ) hours after end of surgery

- Venous blood sample/s will be taken from each subject 24 hours after end of surgery for analyses of Hb, Hct/EVF,  $\text{Na}^+$ ,  $\text{K}^+$ , TPC, CRP, LPC, creatinine and Glomerular Filtration Rate (GFR)/Creatinine Clearance ( $\text{C}_{\text{Cr}}$ ).
- The estimated additional post-operative blood loss volume will be registered in the blood loss log, if applicable.
- Drainages in both treatment groups will be removed.
- Any additional allogeneic blood transfusions will be registered in the allogeneic transfusion log.
- Presence of SIRS will be evaluated
- Vital signs (blood pressure, body temperature and heart rate) will be registered.
- Any additional adverse events and/or medications will be registered in applicable logs.

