**Table 1 Study plan**

|                                              | Screening              | Pre-op                     | Post-op follow up                                                                 |                                      |                                      |                                      |                                      |                     |                            |
|----------------------------------------------|------------------------|----------------------------|-----------------------------------------------------------------------------------|--------------------------------------|--------------------------------------|--------------------------------------|--------------------------------------|---------------------|----------------------------|
| Visit no/sampling time                       | 1                      | 2                          | 3                                                                                 | 4                                    | 5                                    | 6                                    | 7                                    | 8                   | 9                          |
| Visit Description                            | Screening              | Pre-op                     | 3 h                                                                               | Day 1                                | Day 2                                | Day 3                                | Day 4                                | Discharge           | Month 2                    |
| Visit Window
(Hours/days $\pm$ No. Hours) | Before or at admission | Before general anaesthesia | 3h ( $\pm$ 1h), after end of surgery and before post-op transfusion if applicable | 24h ( $\pm$ 6h) after end of surgery | 48h ( $\pm$ 6h) after end of surgery | 72h ( $\pm$ 6h) after end of surgery | 96h ( $\pm$ 6h) after end of surgery | At day of discharge | 8w (5-12w) after discharge |
| Informed consent                             | X                      |                            |                                                                                   |                                      |                                      |                                      |                                      |                     |                            |

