## 3.4 Treatments

### 3.4.1 Identity of investigational product and comparators

The investigational product is the CE-marked Sangvia® Blood Salvage System. The system consists of an intra-operative set, a post-operative set and vacuum tubing that enable collection, filtration and transfusion of intra-operative and post-operative blood.

[figure not shown]

The recommended user instructions for the Sangvia® Blood Salvage System should be followed for set-up, blood collection and reinfusion.

In summary, the collection canister is connected to a suction source with the recommended suction pressure of 100 mmHg (maximum 150 mmHg is allowed) and a suction tip is connected to the inlet tubing of the system. The collection unit is placed lower or at the same height as the operation table and an anticoagulant drip is connected to the system (ACD-A, sodium citrate or CPD) with the recommended ratio of 1:7 (approximately 20 drips per minute). The blood is filtered from larger debris, cement and bone particles by a macro filter of 200µm when collected in the chamber. The upper compartment of the collection unit has a maximum volume of 700 ml and the lower compartment has a maximum volume of 500 ml. When blood is being emptied to the transfusion bag the opening between the upper and the lower compartments should be closed. The blood is filtered from small particles by a micro filter before reinfusion. The reinfusion is initiated when 500 ml blood have been collected or at the end of surgery. Blood transfusion should be completed within 6 hours of the start of collection. Post-operative collection and transfusion will follow after surgery. The post-operative set is set-up and used according to the recommended user instructions. As for the intra-operative collection phase blood transfusion must be completed within 6 hours from start of collection during the post-operative phase. The reinfusion of the post-operatively collected blood may start either when the blood has passed 500 ml in the lower chamber or at the end of the 6 hour collection period. Not more than 2500 ml intra- and/or postoperatively collected blood in total should be transfused to the patients.

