### 3.4.2 Treatment regimens

The subjects included in the study will be randomized to either receive blood transfusion with Sangvia® (test group) or to a group where only allogeneic blood transfusion is used if necessary (control group). In the test group the intra-, and if applicable also the post-operative blood, collected with Sangvia® will always be returned to the patient. In the control group allogeneic blood transfusion will be given if transfusion triggers have been fulfilled and/or if the clinical symptoms justify transfusion. Allogeneic blood transfusion is also allowed to be given in the test group in addition to the Sangvia® blood if transfusion triggers have been fulfilled and/or if the clinical symptoms justify transfusion. Every decision to give allogeneic blood transfusion must whenever possible be taken by an assessor, unaware of the treatment group, and based on his/her opinion of the complete clinical picture for the individual patient. In addition, the reason for a transfusion must always be registered in the CRF.

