### 3.8 Treatment compliance

To ensure treatment compliance the local study personnel must follow the recommended manuals and the instructions in this protocol for the investigational product.

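### Section 3.4.1 lets post-operative reinfusion begin at hour 6, although it requires the same reinfusion to be finished by hour 6

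*Protocol*

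**What the plan says.** Protocol section 3.4.1 describes how the device is used. For the post-operative phase it states the limit as "blood transfusion must be completed within 6 hours from start of collection during the post-operative phase". The following sentence says when the return may begin: either when the blood has "passed 500 ml in the lower chamber or at the end of the 6 hour collection period".

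Four other places bear on this:

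- **Section 3.1**, in the procedures at 3 hours after surgery, says of the test group that "postoperative blood salvage will be stopped, returned and the kit disconnected within 6 hours after activation".
- **Section 3.4.2** says that blood collected with the device "will always be returned to the patient". Section 3.1 allows exceptions only where the investigator sees an increased risk for the individual patient.
- **Section 1.1** gives the purpose of a 6-hour limit: keeping the cells viable and lowering the risk of infection.
- **Section 3.8** says that local staff "must follow the recommended manuals and the instructions in this protocol".

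**The concern.** The two sentences in section 3.4.1 are adjacent and cannot both be met if the second starting point is used. A return that begins when a 6-hour collection period closes cannot already be complete at that moment.

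The patients for whom this matters most are those in the test group whose post-operative drainage does not pass 500 ml. Their blood is to be returned, and the only other start that section 3.4.1 lists for them is hour 6. A site working from that sentence would breach the limit stated one sentence earlier, and that limit exists for a stated safety reason. A site that follows section 3.1 and returns the blood sooner breaches nothing.

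**Working it through.** The protocol gives no numerical result to reproduce here. The check is one of timing, with hours counted from the start of post-operative collection.

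**Inputs**

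- Completion limit: hour 6 (section 3.4.1). Section 3.1 agrees, counting from activation of the kit.
- Permitted starts (section 3.4.1): (a) when 500 ml has been passed, or (b) at the end of the 6-hour collection period, which is hour 6.
- Infusion duration: not stated, and none is assumed.

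**Step 1: time available for infusion**

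Time left = completion limit − start.

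- Start (b): 6 − 6 = 0 hours. Any infusion time above zero breaks the limit.
- Start (a): compliant if 500 ml is reached early enough to finish by hour 6.

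**Step 2: which sentence is wrong**

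Section 3.1 puts stopping, returning and disconnecting all inside 6 hours. That agrees with the completion limit and rules out a start at hour 6, so the late-start clause is the faulty one.

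The intra-operative rule in section 3.4.1 points the same way: "The reinfusion is initiated when 500 ml blood have been collected or at the end of surgery". Its fallback is the end of the operation, an event separate from the 6-hour limit, so it does not place the start on the deadline by construction.

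**Step 3: does an earlier return fit the schedule?**

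Table 1 places the 3-hour (±1 hour) visit "after end of surgery and before post-op transfusion if applicable", and section 3.1 likewise has the blood sample taken before the post-operative return. The sample therefore falls 2 to 4 hours after the end of surgery. Section 3.4.1 says "Post-operative collection and transfusion will follow after surgery", so collection has been running for no longer than the time since surgery ended. The time left after the sample is at least 6 − s hours, where s is the sampling time:

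| Sample taken (h after end of surgery) | Time left to the limit |
|---|---|
| 2 | at least 6 − 2 = 4 h |
| 3 | at least 6 − 3 = 3 h |
| 4 | at least 6 − 4 = 2 h |

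A compliant return can therefore follow the scheduled sample without moving any visit.

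**The case against.** The best defence is that the protocol already settles the matter. The deadline is mandatory while the start is only permitted, and a permission is normally read as subject to the rule before it. Section 3.1 then gives the working instruction clearly. Section 3.4.1 is also presented as a summary of the manufacturer's user instructions, which sites are told to follow and which are not shown. And the 6-hour collection period may be loose shorthand for a window covering both collection and return.

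Much of this limits the consequences. It is fair that a site following section 3.1 would comply, and nothing shows that any site would have transfused late. The investigator may also withhold return from a patient at increased risk.

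None of it removes the fault:

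- A permission that cannot be used without breaking the preceding rule is still wrong.
- On the combined-window reading, the start still falls at the close of the window, with no time left.
- Correct user instructions would leave sites with two conflicting directions, because section 3.8 binds them to the protocol as well as the manuals.
- The exception for individual risk does not cover low drainage volume.
- Section 1.1 words the limit more loosely, without saying that the clock runs from the start of collection, but the operative rules in sections 3.4.1 and 3.1 count from the start of collection and from activation.

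**Conclusion.** The inconsistency is real and minor. Start option (b) leaves 0 hours for infusion, a result that depends only on the protocol's own two time points. The 500 ml option is unaffected. The feasibility figures of at least 4, 3 or 2 hours rest on post-operative collection starting no earlier than the end of surgery, as section 3.4.1 indicates.

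The number of patients affected cannot be stated: post-operative salvage is used only if bleeding continues, and the protocol gives no distribution of drained volumes. This is a wrongly worded treatment instruction with a safety rationale behind it. It is not evidence that blood would in fact be returned late.

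**What to change.** In section 3.4.1, replace the late-start alternative with wording such as: *or otherwise early enough that the reinfusion is finished no later than 6 hours after post-operative collection began (see section 3.1)*. The 500 ml alternative can stay as it is.

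The cost is one phrase in section 3.4.1 and a short note to sites. Visits, data collection and the analysis do not change.

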### 3.4.2 Treatment regimens

The subjects included in the study will be randomized to either receive blood transfusion with Sangvia® (test group) or to a group where only allogeneic blood transfusion is used if necessary (control group). In the test group the intra-, and if applicable also the post-operative blood, collected with Sangvia® will always be returned to the patient. In the control group allogeneic blood transfusion will be given if transfusion triggers have been fulfilled and/or if the clinical symptoms justify transfusion. Allogeneic blood transfusion is also allowed to be given in the test group in addition to the Sangvia® blood if transfusion triggers have been fulfilled and/or if the clinical symptoms justify transfusion. Every decision to give allogeneic blood transfusion must whenever possible be taken by an assessor, unaware of the treatment group, and based on his/her opinion of the complete clinical picture for the individual patient. In addition, the reason for a transfusion must always be registered in the CRF.

### 3.4.3 Labeling

The Sangvia® Blood Salvage System is a CE-marked system with a therefore applicable labeling. The labeling includes:

- “Sangvia® Blood Salvage System, intra-operative autologous blood reinfusion set”/  
“Sangvia® Blood Salvage System, post-operative set”
- “Reference number”
- “Lot number”
- “Expiry date”
- “Sterile”
- “Single use”

The labeling will also include the study code (YA-DRA-0001), “Exclusively for clinical investigation” in local language and name and address of principal investigator and the sponsor.

### 3.4.4 Storage

All investigational products must be kept in a secure place to ensure exclusively use for this clinical study.

### 3.4.5 Accountability

Study products will not be distributed to the investigational site until all agreements between the investigator and Astra Tech are finalized and applicable ethical committee approvals have been obtained and communicated to Astra Tech. Distributed study products will be used only for this study and only in accordance with this Clinical Study Protocol. All product deliveries will be confirmed by the investigator or delegate. All unused study products must be returned to Astra Tech when treatment of the last subject has been completed. Any study product accidentally or deliberately destroyed must be accounted for and discrepancies between amounts dispensed and returned should be explained.

### 3.5 Method of assigning subjects to treatment groups

Each participating clinic will be given a range of Subject ID for use for their included patients. The distribution between clinics will be as follows:

| Clinic No. | Subject ID range | Subject ID range for primary procedures | Subject ID range for secondary procedures |
|------------|------------------|-----------------------------------------|-------------------------------------------|
| Clinic 1   | 1101-1299        | 1101-1199                               | 1201-1299                                 |
| Clinic 2   | 2101-2299        | 2101-2199                               | 2201-2299                                 |
| Clinic 3   | 3101-3299        | 3101-3199                               | 3201-3299                                 |
| Clinic 4   | 4101-4299        | 4101-4199                               | 4201-4299                                 |
| Clinic 5   | 5101-5299        | 5101-5199                               | 5201-5299                                 |
| Clinic 6   | 6101-6299        | 6101-6199                               | 6201-6299                                 |

Subjects will be allocated their Subject ID in a strictly consecutive/sequential order when eligibility for inclusion has been established. Each Subject ID has a corresponding randomization code referring to the appropriate treatment allocation. The randomization process will be performed in a blinded approach, either with a web-based login system or by randomization envelopes that cannot be seen through without opening. If a subject discontinues from the study, the subject number will not be reused, and the subject will not be allowed to re-enter the study. However, during the recruitment period a drop-out subject may be replaced by a new included patient with the Subject ID next in turn in addition to the planned total number of subjects for the specific clinic (see section 6.1.3).

### 3.6 Blinding and procedures for unblinding the study

#### 3.6.1 Methods for ensuring blinding

It is not possible to double blind this study due to the fact that it will be obvious for the study site team to which group the patient has been allocated. I.e. patients in the test group will have their blood collected with the Sangvia® device and in the control group no autologous blood salvage will be performed. The decision of blood bank transfusion will however be assessed in a blinded fashion with an independent assessors unaware of the patient treatment allocation. I.e. each decision of bank blood transfusion will be taken based on transfusion triggers by an assessor unaware of the treatment group whenever possible and the reason/s for the transfusion will be registered. For cases when the decision of bank blood transfusion are taken by a responsible investigator aware of the treatment allocation, e.g. in an emergency situation during surgery, the registered reasons for transfusion will be reviewed by an independent assessor/committee who are unaware of the treatment allocation. Inconsistency in transfusion decision between the independent assessor/committee and the responsible investigator will be reflected in the per protocol analysis where patients with suspected biased transfusion decisions will be excluded. Laboratory sample analyses will be done by assessors unaware of the patient treatment allocation.

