### Primary variable

The choice of the primary variable for efficacy is based upon reported findings in the literature.e.g.6,14,40,41 Need for allogeneic blood transfusion is considered to best reflect the blood loss and transfusion frequency in a patient population while other potential primary variables such as length of hospital stay and post-operative haemoglobin values are multi-factorial dependent on for example preferences of the clinic and gender of the patient etc.

The comparison between the treatment alternatives may be biased as it is almost impossible to blind the study. To mitigate the risk of bias the decision of bank blood transfusion will be taken based on transfusion triggers by an assessor unaware of the treatment group whenever possible and the reason/s for the transfusion will be registered. For cases when the decision of bank blood transfusion are taken by a responsible investigator aware of the treatment allocation, e.g. in an emergency situation during surgery, the registered reasons for transfusion will be reviewed by an independent assessor/committee who are unaware of the treatment allocation. Inconsistency in transfusion decision between the independent assessor/committee and the responsible investigator will be reflected in the per protocol analysis where patients with suspected biased transfusion decisions will be excluded. Also post-operative haemoglobin values will be monitored during the study period. In this way systematically inadequate and/or absent allogeneic blood transfusion decisions will be disclosed and addressed during monitoring visits and concerned patients can be excluded from the Per Protocol analysis.

Bleeding volume or complexity of surgery, i.e. surgery time, are considered to possibly influence outcome of the primary variable why stratification for either primary or secondary/revision hip surgery will be made at each recruiting clinic to ensure equal distribution in the two groups. Subgroup analyses of type (primary and secondary) and complexity (easy < 1 hour, medium 1-2 hours and complex > 2 hours) of surgery are planned to further investigate the correlation between the primary outcome and these factors. Age is also a factor that may have an impact on the outcome of the primary variable. It is however considered that randomization as such will ensure approximately equal age distribution in the two treatment groups. Differences in age

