## 7 STUDY MANAGEMENT

### 7.1 Monitoring

Before first subject enters into the study, a representative of Astra Tech will visit the investigational study site to:

- Determine the adequacy of the facilities
- Discuss with the investigator(s) (and other personnel involved with the study) their responsibilities with regard to protocol adherence, and the responsibilities of Astra Tech or its representatives. This will be documented in a Clinical Study Agreement between Astra Tech and the investigator

During the study, a monitor from Astra Tech or company representing Astra Tech will have regular contacts with the study site, including visits to:

- Provide information and support to the investigator(s)
- Confirm that facilities remain acceptable
- Confirm that the investigational team is adhering to the protocol, that data are being accurately recorded in the CRFs, and that investigational product accountability checks are being performed
- Perform source data verification (a comparison of the data in the CRFs with the subject's medical records at the hospital or practice, and other records relevant to the study). This will require direct access to all original records for each subject (e.g., clinic charts).

The monitor or another Astra Tech representative will be available between visits if the investigator(s) or other staff at the centre need information and advice.

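### Where no blinded assessor decides, the arm-blind review covers only bank-blood transfusions that were given; absent ones are left to sponsor monitoring visits and discretionary per-protocol exclusion

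*Protocol*

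**What the plan says.** Sections 3.1, 3.2 (Primary variable) and 3.6.1 describe one scheme in nearly the same words.

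- **First line.** Each bank-blood decision is to be "taken based on transfusion triggers by an assessor unaware of the treatment group whenever possible".
- **Fallback.** The protocol accepts that the first line will sometimes fail, since "it will be obvious for the study site team to which group the patient has been allocated". The fallback is introduced with "For cases when the decision of bank blood transfusion are taken by a responsible investigator aware of the treatment allocation", and what then happens is that "the registered reasons for transfusion will be reviewed by an independent assessor/committee who are unaware of the treatment allocation". Disagreement leads to exclusion from the per-protocol (PP) set.
- **What is recorded.** Section 3.4.2 says "the reason for a transfusion must always be registered in the CRF". No section asks for a reason when bank blood is not given.
- **Absent transfusions.** Only section 3.2 deals with these. Post-operative Hb is monitored, and "systematically inadequate and/or absent allogeneic blood transfusion decisions will be disclosed and addressed during monitoring visits"; "concerned patients can be excluded from the Per Protocol analysis".
- **Who monitors.** Section 7.1: "a monitor from Astra Tech or company representing Astra Tech will have regular contacts with the study site". The same monitors verify source data and check product accountability. The protocol does not say that they are masked to arm.
- **Which set decides.** Section 6.3 bases efficacy conclusions on the PP set. The All Patient Treated (APT) set includes everyone.

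**The concern.** The trial is open at the site, and its primary outcome is a decision taken by people, partly at their discretion: above 8.5 g/dl the trigger depends on signs of anaemia as the investigator judges them. If an investigator who knows the patient has had salvaged blood holds back bank blood, that patient counts as a success for the device.

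The protocol anticipates this but treats the two directions differently. A questionable transfusion decided unblinded goes to an independent reviewer who does not know the arm. A questionable non-transfusion goes to a monitoring visit, with no stated mask, no rule for what counts as wrongly absent, and exclusion that is optional. At stake are bias in the primary comparison and an efficacy set whose membership can depend on a judgement made with knowledge of the arm.

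**Working it through.** **1. The two routes side by side**

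| | Bank blood given, decision unblinded | Bank blood not given, decision unblinded |
|---|---|---|
| Reason recorded | Yes (3.4.2) | Not required anywhere |
| Reviewer | Independent assessor/committee | Monitor from the sponsor or its contractor (3.2, 7.1) |
| Masked to arm | Yes (3.1, 3.2, 3.6.1) | Not stated |
| Consequence | Excluded from PP if decision disputed | May be excluded from PP |

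**2. The protocol's own sample size.** Inputs from section 6.5: 21% control, 7% test, mean 14%, Z values 1.96 and 1.2816.

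N = (1.96 + 1.2816)² × 4 × 0.14 × 0.86 / 0.14² = 258.2, against 260 stated. This reproduces. Adding 40 for drop-out gives 300, or 150 per arm. No figure in the protocol is wrong on this point.

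**3. How much withholding could matter.** Assumptions, not in the documents: true need is 21% in both arms (no device effect), and a share w of needed transfusions is withheld in the test arm only. The recorded test rate is then 0.21 × (1 − w). The chance of a two-sided Fisher p ≤ 0.05 favouring the device, by exact binomial enumeration, is:

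| w | Recorded test rate | 130 per arm | 150 per arm |
|---|---|---|---|
| 0% | 21.0% | 1.8% | 1.8% |
| 10% | 18.9% | 4.6% | 5.0% |
| 20% | 16.8% | 10.6% | 11.9% |
| 30% | 14.7% | 21.5% | 24.5% |

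At 150 per arm, 21% is 31.5 patients in need, so w = 10% means about 3 withheld transfusions and w = 30% about 9.

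**4. Single-table checks (Fisher, two-sided).** With 27/130 control events and no true effect, 13 withheld test-arm transfusions are needed before the result is significant (14 v 27, p = 0.040). At the planned effect (9 v 27 of 130, p = 0.002), adding back 5 withheld transfusions keeps significance (14 v 27) and adding back 6 removes it (15 v 27, p = 0.063).

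**5. Does PP exclusion repair it?** If every withheld patient is identified and excluded, the test rate becomes 0.21(1 − w) / (1 − 0.21w). At w = 30% this is 0.147 / 0.937 = 15.7%, against 14.7% if they are kept as non-events and a true need of 21%. Exclusion recovers 1.0 of the 6.3 percentage points lost, because it removes patients who should have counted as events.

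**The case against.** The strongest reply is that the first safeguard works in both directions: an assessor unaware of the arm is to take each decision whenever possible, including decisions not to transfuse. The committee is a fallback, and the protocol's example for it is an emergency during surgery. This stands. The gap is confined to decisions not taken blind, and the protocol does not let us estimate how many those will be.

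Section 3.2 also names absent transfusions, section 6.3 treats a wrongful bank-blood decision as a major deviation without limiting it to transfusions given, and laboratory staff are masked, so an Hb at or below the trigger is an objective flag. This stands too: the protocol does not ignore the problem. What remains is who judges the flagged cases, under what mask, and what happens to the patients.

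The phrase about inconsistency in the transfusion decision might be read to include non-transfusion. But the only material named for the committee is the reasons for transfusion, and a withheld transfusion produces none.

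Three stronger readings go beyond the documents:

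- A reader might infer that withholding is **the** bias favouring the device, so that blinded review misses all of it. Over-transfusing controls favours the device as well, and that reaches the committee when the decision was unblinded.
- A reader might infer that monitors know the arm. Accountability checks and source verification make this possible, but the text does not say it; it only fails to say that they are masked.
- A reader might infer that a handful of withheld transfusions is enough to turn the result. That needs a chosen starting point. With an assumed 14% true test rate, 21 v 32 of 150 (p = 0.13) becomes 18 v 32 (p = 0.043) after three withheld decisions. The same rates at 130 per arm with three withheld give 15 v 27, p = 0.063. The protocol's own test-arm assumption is 7%, not 14%.

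**Conclusion.** The point holds in a limited form. Where a blinded assessor does not take the decision, masked review covers only transfusions that were given. Absent transfusions, one of the biases that could favour the device, are left to monitoring visits by sponsor monitors not stated to be masked, with discretionary exclusion from the set on which efficacy conclusions rest.

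Its actual size cannot be derived from the protocol, because neither the share of unblinded decisions nor the share withheld is given. The range of about 5% to 22-25% for a false device-favouring result, against about 2% without withholding, rests on assumed shares of 10% to 30%, equal true need of 21%, and withholding in the test arm alone. Equal withholding in both arms would not produce this bias.

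The protocol does not support saying that absent transfusions go unexamined. It does support saying that they are examined less independently than transfusions given, although the reviewing body needed already exists.

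**What to change.** In sections 3.1, 3.2 and 3.6.1:

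1. List from the CRF, in both arms, every recorded Hb at or below the protocol's own trigger that was not followed by bank blood.
2. Send these cases with arm masked (Hb, vital signs, recorded symptoms) to the same independent assessor/committee, in place of a decision at monitoring visits.
3. Report the number of listed cases and of committee-judged missed transfusions by arm.
4. Keep these patients in an APT analysis of the primary outcome, shown beside the PP result.
5. If a sensitivity analysis is added, count only committee-judged missed transfusions as events. Counting every Hb at or below the trigger would be wrong: the 3-hour sample precedes return of post-operative autologous blood (section 3.1), so a test patient who was low at 3 hours and then needed no bank blood would be scored as a failure. Section 3.1 also combines the triggers with individual clinical considerations, so a low Hb alone does not prove a missed transfusion.

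The cost is a data listing, some extra cases for an existing committee and one further table. The committee would judge without a stated reason for not transfusing unless a CRF field is added for it. The listing sees only the scheduled samples (3 hours, days 1, 2 and 4) and cannot detect symptom-based withholding above the trigger, so the gap is narrowed but not closed.
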